## Abstract

**Background:**

The focus in recent years on physical inactivity and metabolic disturbances in individuals with schizophrenia raises the question of potential effects of physical activity. Physical activity has shown beneficial effects on cognition in healthy older individuals as well as on symptom severity in depression. However, opinions diverge regarding whether aerobic high-intensity interval training reduces cognition and key symptoms in schizophrenia. The main objective for the trial is to investigate the potential effects of aerobic high-intensity interval training on neurocognitive function and mental symptoms in outpatients with schizophrenia.

**Methods/Design:**

The trial is designed as a randomized controlled, observer-blinded clinical trial. Patients are randomized to 1 of 2 treatment arms with 12-week duration: aerobic high-intensity interval training or computer gaming skills training. All participants also receive treatment as usual. Primary outcome measure is neurocognitive function. Secondary outcome measures will be positive and negative symptoms, wellbeing, tobacco-smoking patterns and physiological/metabolic parameters. Patient recruitment takes place in catchment area-based outpatient clinics.

**Trial registration:**

ClinicalTrials.gov NCT02205684. Registered 29 July 2014.

## Background

Schizophrenia is a severe mental illness characterized by delusions and hallucinations (i.e. positive symptoms), affect flattening, poverty of speech, lack of motivation and social withdrawal (i.e. negative symptoms) and cognitive impairment, making it one of the leading causes of disability in the age group 15–44 years [1–3].

People with schizophrenia are more likely to smoke [4], to be physically inactive [5], suffer from malnutrition due to an unhealthy diet [6] and have low cardiorespiratory fitness (CRF) [7–9]. They commonly also suffer from comorbid psychiatric disorders such as depression as well as substance misuse [10] and manifest multiple somatic comorbidities [11]. Compared to healthy individuals there is a 2.5 to 4.0-fold increase in prevalence of the metabolic syndrome [12–14] and a 20 % reduction in life expectancy in individuals with schizophrenia.

Antipsychotic medication is a cornerstone in the treatment of schizophrenia, substantially reducing symptom severity and relapses [15]. However, antipsychotics are most effective in reducing positive symptoms, and they have minimal effect on negative symptoms or cognitive function [16]. Psychosocial interventions (e.g. cognitive behavior therapy, cognitive remediation therapy, family psychoeducation, social skills training, supported employment) are usually provided in addition to pharmacological treatment and play an important role in the treatment of schizophrenia, especially in improving daily life functioning.

Among healthy individuals, physical activity has positive effects on physical health, mental health and cognition. Moreover, positive effects of physical activity have also been described for persons with mental disorders, such as depression [17–20]. High-intensity interval training is shown to increase CRF and reduce the risk of various somatic illnesses [21, 22] and is established as a safe and useful exercise method. For people with schizophrenia evidence is sparse with regard to the effect of physical activity, in particular on post-exercise psychological states or neurocognition. A recent randomized controlled trial (RCT) investigated the effect of an aerobic exercise program in 33 individuals with schizophrenia (aerobic exercise, *n* = 16; treatment as usual, *n* = 17) [23]. After completion of the 12-week exercise program (1 hour each session, 3 times weekly) the aerobic exercise group showed a significant improvement compared to the control group. The effects of combined interventions were examined in a non-randomized study of 43 individuals with schizophrenia [24]. The participants were exposed to either endurance training (*n* = 22) or a control condition playing table soccer (*n* = 21). During the last half of the 12-weeks intervention the individuals in both groups also attended a cognitive remediation program. Significant improvements were found in short-term and long-term verbal memory and cognitive flexibility from the start of the combined intervention at week 6 to the end of the 3-month training period in the group exposed to endurance training augmented with cognitive remediation. However, conclusions concerning the effects of each component in the combined intervention are hard to draw due to the design of the study.

Recent reviews have called for well-designed studies to explore these important topics further [25–27]. Interpretation of previous studies investigating effects of regular sport activities lasting for weeks or months have been hampered by small sample sizes [28–30]. In the largest study to date, 20 patients with schizophrenia met compliance demands and received exercise therapy 1 to 2 hours a week for 6 months in the experimental group. When compared to 19 patients in the control condition receiving occupational therapy [8] significant effects were found on positive and depressive symptoms, as well as trend level decrease for negative symptoms in per protocol analyses. The total attrition rate was 38 %, and in the intention-to-treat analysis no significant effects were found.

The cardiovascular fitness hypothesis [31] suggests that CRF is a physiological mediator that explains the various mental health benefits of physical activity. In regard to cognitive functions, CRF might be more beneficial for individuals with limits on their cognitive reserves [32], such as people with schizophrenia. A finding of exercise-induced increase in hippocampal volume in patients with schizophrenia and a positive correlation of volume increase and short-term memory improvement supports this hypothesis [33].

Low CRF increases the risk of cardiovascular disease (CVD) [34, 35], which is the largest single cause of death in schizophrenia [36]. This, taken together with an unhealthy lifestyle, underscores the need for multi-disciplinary treatment and underlines the need for addressing physical activity and, in particular, high-intensity interval training, which is more effective than moderate intensity exercise in increasing CRF in the short term [37, 38].

Many exercise intervention studies for persons with mental disorders have methodological limitations, which makes it difficult to draw firm conclusions. The most common limitations are small sample sizes, that the randomization process has not been undertaken at a site remote from where the intervention takes place, lack of blinded assessment of outcome, imprecise assessments (if any) of CRF, low adherence to the exercise protocols, lack of long- term follow-up assessment, and not analyzing the data according to the intention-to-treat principle [39].

There is currently insufficient evidence to know whether regular high-intensity interval training reduces key symptoms in schizophrenia. Studies with larger sample sizes comprised of participants adhering to the exercise protocol are needed.

We aim to conduct a trial where these methodological considerations are addressed by comparing a 12-week aerobic high-intensity interval training (HIIT) program to skills training of the same duration, with regard to: 1) aspects of cognitive function, especially memory, attention and executive function, and 2) psychiatric symptom load (negative and positive symptoms) and wellbeing. Post-treatment improvement in cognition and psychotic symptoms are anticipated. We hypothesize that the individuals in the Exercise Group (EG) will perform better than individuals in the Computer Skills Group (CSG) on aspects of cognitive function, especially memory, attention and executive function. In addition, we expect ameliorated positive and negative symptoms in the EG.

The effects of HIIT on maximum oxygen uptake and risk factors for CVD (i.e. tobacco- smoking, elevated blood pressure, dyslipidemia, insulin resistance and high body fat) are also subject to investigation.

## Methods

### Trial design

This trial is designed as a randomized controlled, parallel group, observer-blinded clinical trial (Fig. 1).

**Fig. 1 Fig1:**
[figure not shown]
Flow chart – participants in the Effects of Physical Activity in Psychosis (EPHAPS) trial

Participants are randomized to either a high-intensity interval group (Exercise Group, EG) or to a comparison group (Computer Gaming Skills Group, CSG). During the 12-week interventions treatment as usual is continued for all patients. Patients are assessed at the start (T_0_) and end of the intervention (T_1_) as well as at 4 months post-treatment (T_2_). The trial is observer-blinded, as measurement of psychiatric symptoms and neurocognitive function is performed by research staff blinded for group allocation. The researchers are geographically dispersed from the training facilities. When assessed after training, the participants are instructed not to disclose what activity they have taken part in. The physiological testing is performed by staff involved in delivery of the interventions and will not be blinded except at baseline. The same holds for collecting self-ratings involving measures of activity.

### Recruitment and eligibility

The participants are outpatients at the psychiatric rehabilitation clinics in Tønsberg (Nordre Vestfold distriktspsykiatriske senter, NVDPS) and Larvik (Søndre Vestfold distriktspsykiatriske senter, SVDPS) in Vestfold County. The clinics are part of the Division of Mental Health and Addiction in Vestfold Hospital Trust, Norway. The outpatient clinics are catchment area-based and cover a total population of approximately 200,000 people. Patient inclusion started in August 2014 and will continue until October 2016. Eligible for the study are outpatients who fulfill the *Diagnostic and Statistical Manual of Mental Disorders* (DSM-V) criteria for schizophrenia spectrum disorder (schizophrenia, schizoaffective disorder and schizophreniform disorder). Inclusion and exclusion criteria are presented in Table 1. Participation will be terminated if any of the exclusion criteria occurs (for instance pregnancy) during the trial or if the participant withdraws the informed consent.

**Table 1 Tab1:** Inclusion and exclusion criteria

*Inclusion criteria*
Age between 18 and 67
Understand and speak a Scandinavian language
Fulfill the DSM-V criteria for schizophrenia spectrum disorder (schizophrenia, schizoaffective disorder and schizophreniform disorder)
*Exclusion criteria*
Pregnancy
Chest pain during exercise
Unstable angina pectoris
Recent myocardial infarction
Uncontrollable cardiac arrhythmia
Severe hypertension (>180/110 mmHg)
Comorbid diagnosis of mild mental retardation
Medical conditions incompatible with participation

*DSM Diagnostic and Statistical Manual of Mental Disorders*

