### Intervention

The exercise sessions will be conducted at the Buskerud and Vestfold University College and the computer gaming at a local high school in Tønsberg. Supervision of participants in the two groups is carried out by the same personnel employed in the outpatient clinics and dedicated to the project throughout the data collection period. The time spent with activities, as well as time spent with the intervention staff, is the same in both groups, and a specific time schedule is followed by the staff to ensure that each session in the exercise and comparison groups last 45 minutes. Participants in both groups are also accompanied by the project personnel during transportation, during the sessions of the intervention and during breaks.

The exercise sessions consist of supervised walking/running on a treadmill twice per week for 12 weeks. Each session will have the following structure; 8-minute warm-up, followed by 4x4 minute intervals with 85–95 % of maximum heart rate, with active pauses of 3 minutes walking/running at approximately 70 % of maximum heart rate. Heart rate will be measured and controlled continuously throughout the exercise session by research personnel with a heart rate monitor (RCX3 heart monitor from Polar (Polar Electro Oy, 90440 Kempele, Finland)) to ensure that the participants intervals and active pauses are performed with the desired intensity. The exercise session will end with a 5-minute cool-down period. The goal is to have the participants adhere to the protocol. However, we realize that some participants might have difficulties with this intensive program in the beginning of the intervention, and, thus, the protocol will be individualized and progressive both in terms of the number of intervals and the intensity. This high-intensity exercise performed as 4x4 minute intervals has previously been shown to be feasible, safe and effective for individuals with schizophrenia [41] and other clinical populations [21, 22, 26, 27, 38].

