Participants in the comparison group take part in sessions performing computer-simulated sports activities (Nintendo Wii Sports (Nintendo, Frankfurt am Main, Germany) tennis, baseball, golf, bowling). Physiological responses (i.e. oxygen consumption, cardiac output, metabolic rate) of Nintendo Wii tennis (and baseball) has shown to be lower than brisk treadmill walking when tested in bouts of 10 minutes [42]. Through comparing neurocognitive and symptom scores in a group that is physically active with the performance of a group that simulates such activity, we expect to be able to extract the net effect of high-intensity exercise. Changes in simulated sports skills are monitored and continuous feedback is given to the participants by supervising personnel.

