#### Cardiorespiratory fitness, physical activity and sleeping habits

Maximal oxygen uptake (VO_2max_) is measured during a maximum exercise test on a treadmill using a modified Balke protocol [56]. Gas exchange is sampled continuously into a mixing chamber every 30 s by having the participants breathe into a Hans Rudolph 2-way breathing valve (2700 series, Hans Rudolph Inc., Kansas City, MO, USA) connected to a Jaeger Oxycon Pro gas analyzer (Erich Jaeger GmbH, Hoechberg, Germany), which measures the oxygen and carbon dioxide content.

Physical activity level is measured both objectively (ActiGraph accelerometer GT3X+ (ActiGraph, Pensacola, FL, USA) worn on the hip for 4 consecutive days; 2 weekdays and 2 days of the weekend) and subjectively using the International Physical Activity Questionnaire (IPAQ, short form [57, 58]). In addition, potential psychosocial mediators for change in physical activity and attitudes towards physical activity will be measured by previously developed and validated scales: social support for physical activity [59, 60], self-efficacy and outcome expectancies and attitudes [61, 62]. Sleeping habits are assessed using the ActiGraph data as well as the brief Insomnia Severity Index (ISI, [63]).

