### Protocol deviations

When absent from scheduled exercise or computer gaming, the participant will be contacted and offered to participate on a following day the same week. Participants who fail to complete at least 60 % of the total number of intervention sessions or have not participated for more than 2 successive weeks are considered protocol violators. Participants who are unable to meet for the VO_2max_ test within 10 days following the last training session will also be considered protocol violators. However, they will be allowed to stay in the study and will be tested as soon as possible, as well as invited to take part in T_2_. Statistical analyses will be performed both based on the principle of “intention-to-treat” including everyone regardless of protocol violations, but “per protocol” analyses will also be executed, comparing only those who completed the two treatment conditions according to the protocol.

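### Ending participation, not only the assigned activity, when an exclusion criterion appears after randomisation stops outcome collection and weakens the intention-to-treat analysis

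*Protocol article*

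**What the plan says.** All places are in the protocol article.

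- **Recruitment and eligibility:** "Participation will be terminated if any of the exclusion criteria occurs (for instance pregnancy) during the trial". The same sentence gives withdrawal of informed consent as the other ground for termination.
- **Table 1:** the exclusion criteria include "Chest pain during exercise" and "Medical conditions incompatible with participation", alongside pregnancy, cardiac conditions, severe hypertension and mild mental retardation.
- **Protocol deviations:** the intention-to-treat analysis is described as "including everyone regardless of protocol violations". Of protocol violators the section says that "they will be allowed to stay in the study and will be tested as soon as possible", and that they are invited to T2. On its narrowest reading that sentence covers only those who are late for the VO2max test.
- **Sample size calculations:** 15 % dropout after randomisation is expected, and attrition at later stages is left to the intention-to-treat analysis.
- **Statistical analysis:** the named methods are MANOVA and repeated measures ANOVA.
- **Emergency procedures:** for symptoms such as chest pain during exercise, the session is stopped. Nothing is said about ending participation.
- **Treatment as usual:** a participant admitted to an inpatient unit during an exacerbation remains in the project.

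The article nowhere says that a participant terminated under the eligibility rule is still assessed at T1 or T2.

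**The concern.** Stopping an activity and stopping measurement are different decisions, and the rule takes both at once. The cognitive battery, the PANSS and the questionnaires need no exertion, so nothing stated explains why pregnancy, for example, should end cognitive testing.

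Two things are at stake. First, an intention-to-treat analysis needs outcomes on the people randomised. A missing-data method can model outcomes that were never collected but cannot recover them, and the rule on collection is set here, in the protocol. Second, the reason for the loss is a change in health, and for some criteria that change can depend on the assigned activity. If loss differs by arm and is related to outcome, the comparison of those who remain is biased, and a larger sample does not remove that bias.

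The Background section lists failure to analyse by intention to treat among the common weaknesses of earlier exercise trials, and the authors say that this trial addresses those weaknesses. The rule works against that aim.

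**Working it through.** **Step 1. The rules side by side.**

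| Event after randomisation | Place | Consequence stated |
|---|---|---|
| Too few sessions, long absence or late VO2max test | Protocol deviations | Protocol violator, included in intention to treat; retention and testing stated (at the least for late VO2max testers) |
| Psychiatric exacerbation with admission | Treatment as usual | Continues in the project |
| Chest pain during exercise | Emergency procedures | Session stopped |
| Chest pain during exercise | Recruitment and eligibility with Table 1 | Participation terminated |
| Any other exclusion criterion | Recruitment and eligibility | Participation terminated |

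The two rows on chest pain give different consequences for one event. The last row has no provision for continued assessment.

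**Step 2. What is lost.** Termination before T1 removes T1 and T2. Termination between T1 and T2 removes T2 only. In their standard form the named ANOVA methods use only participants with the outcome at each time point analysed, so these people would drop out of the affected comparisons.

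**Step 3. Can the loss differ by arm?**

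- *For a difference:* the exercise arm has "supervised walking/running on a treadmill twice per week for 12 weeks", that is 2 × 12 = 24 planned sessions, with intervals at 85–95 % of maximum heart rate. The comparison arm plays simulated sports, and for tennis and baseball the article cites physiological responses "lower than brisk treadmill walking when tested in bouts of 10 minutes". Whether a condition is incompatible with participation can depend on which activity was assigned.
- *Against a difference:* maximal oxygen uptake "is measured during a maximum exercise test on a treadmill using a modified Balke protocol" at T0, T1 and T2 in both arms. The T0 test precedes randomisation, as do the ECG and the physician's examination. Training is individualised and progressive. Pregnancy has no evident link to arm.

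**Step 4. Size, on assumed values.** The plan gives no termination rate, so there is no figure of its own to reproduce on this point. The one input taken from it is the 0.50 SD target. Let pE and pC be the shares terminated in the exercise and comparison arms, and let terminated participants do d SD worse than completers. In each arm the full mean equals the completer mean minus p × d, so

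bias in the completer difference = d × (pE − pC).

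| pE, pC (assumed) | d = 0.25 | d = 0.5 | d = 1.0 |
|---|---|---|---|
| 5 %, 2 % | 0.0075 | 0.015 | 0.03 |
| 10 %, 2 % | 0.02 | 0.04 | 0.08 |
| 15 %, 5 % | 0.025 | 0.05 | 0.10 |

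The range is about 0.01 to 0.10 SD. As a share of the target it runs from 0.0075/0.50 = 1.5 % to 0.10/0.50 = 20 %. If pE = pC the bias is zero. If terminated participants would have done better than completers, the sign reverses.

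**Step 5. Scale.** With 55 per arm the standard error of the difference is √(2/55) = 0.19 SD, so the top of the range is about half a standard error.

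**Step 6. Power.** Take 126/2 = 63 randomised per arm, a two-sided 5 % level and power = Φ(0.5/√(1/nE + 1/nC) − 1.96). Loss of 15 % in both arms gives 73.5 %, 20 % against 15 % gives 72.2 %, and 25 % against 15 % gives 70.7 %. An extra five points of loss in one arm therefore costs about 1.3 to 1.5 points of power. The 73.5 % starting value falls short of the planned 80 % for reasons in the sample-size calculation that are separate from this point.

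**The case against.** The strongest reply is that two rules for two groups do not conflict. The protocol violators in the Protocol deviations section are defined by attendance and by the timing of the VO2max test. The eligibility rule concerns emergent ineligibility and withdrawn consent. Some dropout is already budgeted, and the handling of missing scores is commonly left to an analysis plan, which is not shown here. This stands in part. A reader might infer that the article literally contradicts its intention-to-treat definition, and it does not. The clash is one of substance: everyone is to be analysed, while the article orders that some people stop being measured.

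A reader might also infer that the exercise arm will lose more people and that this will favour exercise. The documents do not show either. Maximal testing before allocation should find many people prone to chest pain on exertion, and both arms are tested maximally again. Nothing says that those terminated would have changed less on the cognitive battery. Unequal loss is a possibility created by the design, and its size may be small.

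Two further inferences go beyond the text. The article does not say who judges incompatibility after randomisation, so it cannot be said that people who know the arm make that judgement. Nor does the rule conceal poor tolerability: the Ethical considerations section commits to CONSORT reporting, under which terminations would be shown.

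**Conclusion.** The point holds as a fault in a stated rule. As written, the rule ends outcome collection for consenting, randomised participants whenever an exclusion criterion appears. That weakens the intention-to-treat analysis and the reliance on it for attrition, and it leaves Recruitment and eligibility out of step with Protocol deviations and with Emergency procedures.

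This conclusion rests on reading the ending of participation in its plain sense, which the pairing with withdrawn consent supports. It does not depend on any assumed rate. The illustrative 0.01 to 0.10 SD does: it assumes termination of 5–15 % in the exercise arm against 2–5 % in the comparison arm, with terminated participants 0.25 to 1.0 SD worse than completers. None of these values is in the documents. The effect could be negligible, but the change is cheap enough that it should be made.

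**What to change.** Reconcile Recruitment and eligibility, Protocol deviations and Emergency procedures by stating two things separately:

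1. When the assigned activity ends. This remains the sponsor's clinical decision, and no change to it is proposed here.
2. When outcome assessment ends: only on withdrawal of consent.

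Participants whose activity is stopped would still be invited at T1 and T2 to the assessments that need no exercise: the MCCB and PANSS by blinded raters, and the questionnaires. They would be analysed in the arm to which they were randomised.

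The cost is a short amendment and a few visits within the existing schedule. For people terminated before the amendment, the number, arm, timing and reason should be reported.
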